#### Secondary outcome measures

In further measurements, changes in inflammation, bone turnover, bone mineral density (BMD), insulin resistance, blood pressure, body fat mass, stage of liver stiffness and steatosis, and mental health (improvement of depression) will be investigated. Furthermore, we will assess the adipose depot vitamin D concentrations and expression of enzymes (25-hydroxylases such as CYP27A1, CYP2R1, CYP2J2, CYP3A4, CYP2C11, and CYP27B1, as well as 24-hydroxylase CYP24A1) and vitamin D receptor in subcutaneous tissue (SAT), visceral adipose tissue (VAT), and liver tissue samples collected during surgery. Additionally, the liver tissue samples will be used in addition to the prescribed study-related measures for a histological examination as extended diagnostics for NAFLD or non-alcoholic steatohepatitis and molecular analysis to further evaluate disease specific mechanisms [62, 63].

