#### Laboratory parameters

*Vitamin D status*: 25-OHD (nmol/L), 1,25-dihydroxy vitamin D (pg/ml)*Biochemical parameters*: sodium (nmol/L), potassium (nmol/L), chloride (nmol/L), calcium (nmol/L), magnesium (nmol/L), iron (μg/dl), total protein (g/L), albumin (g/L), triglyceride (mg/dl), total cholesterol (mg/dl), high-density lipoprotein (mg/dl), low-density lipoprotein (mg/dl), vitamin B_12_ (pmol/L), folic acid (nmol/L), vitamin A (μmol/L), vitamin E (μmol/L), ferritin (μg/L), transferrin (mg/dl), and transferrin saturation (%)*Bone turnover markers*: calcium (mmol/L), osteocalcin (ng/ml), bone-specific alkaline phosphatase (U/L), type I collagen cross-linked C-terminal telopeptide (ng/ml), anorganic phosphate (mmol/L), parathyroid hormone intact (pg/ml), and amino-terminal propeptide of type I procollagen (ng/ml)*Inflammation markers*: C-reactive protein (mg/dl) and interleukin 6 (pg/ml)*Insulin resistance markers*: C-peptide (ng/ml), insulin (μU/ml), blood glucose (mg/dl), and glycosylated hemoglobin HbA1c (%)*Liver parameters*: aspartate transaminase (U/L), alanine transaminase (U/L), γ-glutamyl transpeptidase (U/L), total alkaline phosphatase (U/L), and cholinesterase (U/L)Blood count*Coagulation*: Normotest (%) (Technoclone, Vienna, Austria), activated partial thromboplastin time (s), and fibrinogen (mg/dl)*Protein electrophoresis*: serum protein electrophoresis, haptoglobin (mg/dl), and α_2_-macroglobulin (mg/dl)

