### Statistical analysis

Data exploration using descriptive statistical analysis and inferential statistics (uni- and multivariate) will be performed. The data will be described by frequencies or percentages, means and standard deviations, medians and confidence intervals, and graphics. For proofing of normal distributions, visual inspection of histograms or box plots will be used. Independent samples *t* tests, Mann–Whitney *U* test or *χ*^2^ tests will be performed to compare groups. Correlation coefficients will be used with respect to the secondary outcomes. Analysis of covariance will be used to compare parameters at baseline and after the intervention (postoperatively), as well as after the follow-up, between intervention and control groups, adjusting for the baseline value as a covariate. IBM SPSS Statistics for Windows version 22 software (IBM, Armonk, NY, USA) will be used for all statistical analyses. All tests are two-sided, and a *p* value <0.05 is considered statistically significant.

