## Discussion

The major strengths of the proposed study are the prospective, randomized, double-blind, placebo-controlled design and the implementation of an independent evaluation of outcome parameters. The expected result, positive or negative, should provide an evidence-based and potentially optimal treatment of vitamin D deficiency following bariatric surgery and should define the interactions of vitamin D and specific factors, such as liver and bone health, inflammation, insulin resistance, blood pressure, depression symptoms, microbiota, and weight loss. Furthermore, as far as we know, the LOAD study is one of the first trials with this type of vitamin D supplementation in bariatric patients.

Some aspects of the study design, however, may deserve a closer discussion. Why was an active treatment regime after the loading dose chosen for the control group? From an ethical point of view, and bearing in mind the importance of vitamin D for bone metabolism, it would be difficult not to provide these patients with vitamin D supplementation at all. Therefore, we decided to use the placebo only for the loading dose (in the first postoperative month) to compare this dosing regimen with the usual supplementation. Indeed, with this study design, we expect to treat and provide supplements to the patients more effectively than in routine care.

The prospective benefit will have a positive impact on vitamin D status and therefore on the well-being and health-related quality of life, which has been described in the literature [79–81]. A further question might be why a supplementation regimen different from an established treatment of vitamin D deficiency in bariatric patients was chosen. In fact, from a methodological point of view, a constant daily supplementation of vitamin D would be preferable. However, there is evidence in the literature that this standard supplementation in bariatric patients is not sufficient, and with this novel dosing regimen, the final vitamin D plateau could be achieved earlier than the four half-lives required when administered only at the maintenance dose rate [65]. Another important point for the success of the LOAD study is the compliance of the participants regarding regular study visits. Hence, we are in close contact with the participants, and they are receiving text messages before the scheduled appointment.

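### The p < 0.05 rule for all tests gives about 20 unranked secondary measures at two time points the status of significance tests; chance findings are likely if none is truly affected

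*Protocol article*

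**What the plan says.** Under Statistical analysis, the protocol article states "All tests are two-sided" and that a p "value <0.05 is considered statistically significant". The rule does not separate the primary from the secondary outcomes. The same section plans analysis of covariance on the parameters "at baseline and after the intervention (postoperatively), as well as after the follow-up, between intervention and control groups", adjusted for the baseline value. That gives two post-baseline comparisons, at week 24 and at week 48. Correlation coefficients are planned for the secondary outcomes as well.

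Under Secondary outcome measures, the article lists "changes in inflammation, bone turnover, bone mineral density (BMD), insulin resistance, blood pressure, body fat mass, stage of liver stiffness and steatosis, and mental health", in no order and with none marked as key. Tissue analyses follow. Laboratory parameters breaks some of these domains into individual markers; inflammation, for example, is "C-reactive protein (mg/dl) and interleukin 6 (pg/ml").

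The Sample size calculation rests on one endpoint only, 25-OHD at 24 weeks. The Discussion says that the expected result "should define the interactions of vitamin D and specific factors, such as liver and bone health, inflammation, insulin resistance, blood pressure" and several further factors.

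**The concern.** A p value below 0.05 on any one of many secondary tests would, under the stated rule, count as statistically significant, and nothing in the article says that such results are to be read differently from the primary result. With many tests, some will cross the threshold by chance.

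The size of the trial makes this matter more. With 25 per group and no dropout, an unadjusted t test reaches p < 0.05 only when the observed difference exceeds about 2.01 × √(2/25) = 0.57 standard deviations. A chance finding on bone, liver, inflammation or mood would therefore look like a sizeable effect, in a trial that was not powered for any of these outcomes.

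**Working it through.** **The plan's own figure.** The article gives no family-wise error rate. Its only error calculation is the sample size for the primary endpoint: difference 30 nmol/L, SD 35 nmol/L, two-sided 0.05, 80% power. The normal approximation gives n = 2 × (1.960 + 0.842)² × (35/30)² = 21.4, so 22 per group, as stated. (The t test gives 22.4, so 23; power at 22 is 79.3%.) That calculation covers one test, and its 0.05 applies to that test alone.

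**Number of secondary measures**, from Secondary outcome measures and Laboratory parameters:

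| Domain | Measures |
|---|---|
| Inflammation (C-reactive protein, interleukin 6) | 2 |
| Bone turnover | 7 |
| Bone mineral density | 1 |
| Insulin resistance (C-peptide, insulin, glucose, HbA1c) | 4 |
| Blood pressure (systolic and diastolic, assumed) | 2 |
| Body fat mass | 1 |
| Liver stiffness and steatosis | 2 |
| Depression score | 1 |
| **Total** | **20** |

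The five liver enzymes, microbiota, tissue measures and correlation coefficients are left out and would add to the count.

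**Number of tests.** 20 measures × 2 time points = 40. The Measurements section, however, says that blood pressure, depression symptoms, bone mineral density and fat mass are measured twice. Read literally, these five measures have one post-baseline value each: 15 × 2 + 5 × 1 = 35 tests. Table 2 disagrees, with DEXA at three visits and the depression inventory at five. The exact count is therefore uncertain.

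**Expected chance findings if no secondary measure is truly affected.** 40 × 0.05 = 2.0, or 35 × 0.05 = 1.75. Correlation does not change these expectations.

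**Probability of at least one p < 0.05 under independence**, 1 − 0.95^k:

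- k = 20 (one time point): 64.2%
- k = 35: 83.4%
- k = 40: 87.1%
- k = 16 (one test for each of 8 domains, two time points): 56.0%

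**With correlation.** The article gives no correlations, so the values below are assumptions. Test statistics for 20 measures at two time points were simulated as multivariate normal (40,000 to 60,000 draws, two-sided 0.05, all nulls true).

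| Assumed structure | P(at least one) |
|---|---|
| Domain blocks: within-domain 0.3 to 0.8, between-domain 0 to 0.2, across time 0.5 to 0.8 | 63% to 83% |
| Uniform 0.5 among all measures, across time 0 to 0.8 | 57% to 66% |
| Uniform 0.7 among all measures, across time 0 to 0.8 | 41% to 50% |

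A uniform 0.7 is hard to credit across C-reactive protein, bone density, blood pressure and a depression score, so the last row serves as a low bound for 40 tests. It is still about eight times the nominal 5%.

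**The case against.** The strongest objection is that ranking secondary outcomes and labelling them exploratory is normal content for a statistical analysis plan. This is a condensed article, and its threshold may be only a routine nominal level per test. A plan that is not shown could restrict the secondary claims. This stands in part: silence on multiplicity alone would be no finding. But the article is not silent. It states a significance rule and applies it to all tests, and a later restriction would have to override that sentence. The opening reference to data exploration does not limit the rule either, because it covers descriptive and inferential work together, the primary included.

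Second, the article does separate one powered primary endpoint from the further measurements. That is correct, and it disposes of a stronger reading that a reader might infer: that multiplicity inflates the error of the main conclusion. It does not. The primary is one comparison at one time point.

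Third, a reader might take 87% as the probability of a false claim. The article does not support that. The figure needs independent tests and every secondary null true, and the seven bone markers, the four insulin-resistance markers and repeated values in the same patients are clearly related. A nominal p < 0.05 is also not yet a published claim.

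Fourth, the Discussion's verb could be read as a commitment to confirmatory claims. It is a statement of expectation, not an analysis rule, and the article's closing lines are more cautious. Softening it would be editorial.

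**Conclusion.** The point holds as a cheap improvement. The article calls p < 0.05 statistically significant for all tests, and so gives about 20 unranked secondary measures at two time points the same standing as the primary.

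If the loading doses affect none of them, about 2 of 40 tests (1.75 of 35) would be expected to cross the threshold. At least one would do so with probability 87% at most for 40 tests, more plausibly 63% to 83%, and 41% to 50% under strong uniform correlation. The count rests on treating blood pressure as two measures and on two post-baseline tests per measure; the ranges below 87% rest on assumed correlations. Under every structure considered for these 40 tests, the risk is many times 5%.

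The week-24 25-OHD comparison, its significance level and its sample size are untouched. The article also does not show that unadjusted secondary testing is wrong in itself; it is acceptable when the results are presented as exploratory.

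**What to change.** In Statistical analysis, restrict the p < 0.05 significance rule to the week-24 25-OHD comparison between groups. State that all secondary outcomes will be reported as baseline-adjusted differences with 95% confidence intervals, labelled exploratory, and will not be used for claims of significance. The planned analysis of covariance already supplies these estimates.

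Optionally, if a secondary claim is wanted, name one or two key secondary outcomes, each with its time point, and test them in fixed order only after a significant primary result. This should be settled before the treatment allocation is revealed.

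The cost is wording only: no further patients, visits or data. The downside is that fewer secondary results can be called significant.

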## Discussion

The major strengths of the proposed study are the prospective, randomized, double-blind, placebo-controlled design and the implementation of an independent evaluation of outcome parameters. The expected result, positive or negative, should provide an evidence-based and potentially optimal treatment of vitamin D deficiency following bariatric surgery and should define the interactions of vitamin D and specific factors, such as liver and bone health, inflammation, insulin resistance, blood pressure, depression symptoms, microbiota, and weight loss. Furthermore, as far as we know, the LOAD study is one of the first trials with this type of vitamin D supplementation in bariatric patients.

Some aspects of the study design, however, may deserve a closer discussion. Why was an active treatment regime after the loading dose chosen for the control group? From an ethical point of view, and bearing in mind the importance of vitamin D for bone metabolism, it would be difficult not to provide these patients with vitamin D supplementation at all. Therefore, we decided to use the placebo only for the loading dose (in the first postoperative month) to compare this dosing regimen with the usual supplementation. Indeed, with this study design, we expect to treat and provide supplements to the patients more effectively than in routine care.

The prospective benefit will have a positive impact on vitamin D status and therefore on the well-being and health-related quality of life, which has been described in the literature [79–81]. A further question might be why a supplementation regimen different from an established treatment of vitamin D deficiency in bariatric patients was chosen. In fact, from a methodological point of view, a constant daily supplementation of vitamin D would be preferable. However, there is evidence in the literature that this standard supplementation in bariatric patients is not sufficient, and with this novel dosing regimen, the final vitamin D plateau could be achieved earlier than the four half-lives required when administered only at the maintenance dose rate [65]. Another important point for the success of the LOAD study is the compliance of the participants regarding regular study visits. Hence, we are in close contact with the participants, and they are receiving text messages before the scheduled appointment.

Finally, one might assume that the rather small sample size of 50 bariatric patients in the proposed study might be underpowered to detect a significant difference between groups. However, the study is powered to detect differences between the groups for 24-week serum 25-OHD levels, with a given clinically relevant difference of 30 nmol/L and a standard deviation of 35 nmol/L of the differences. Thus, if high-dose supplementation with vitamin D is indeed effective, a reduction of vitamin D deficiency after 24 weeks would not be unrealistic.

In conclusion, this vitamin D supplementation regimen has the potential to be a safe, orally available, cheap, and evidence-based treatment of low vitamin D status following bariatric surgery in this increasingly prevalent group, and the study probably also is an opportunity to find an association between obesity and vitamin D deficiency.

## Trial status

The LOAD study commenced recruitment in April 2014. Recruitment was completed in April 2015.

## Abbreviations

BDI: Beck Depression Inventory
BIA: Bioelectrical impedance analysis
BMD: Bone mineral density
BMI: Body mass index
CAP: Controlled attenuation parameter
DEXA: Dual-energy X-ray absorptiometry
EFSA: European Food Safety Authority
GFR: Glomerular filtration rate
LOAD: Link between Obesity And Vitamin D in bariatric patients with omega-loop bypass surgery
MCT: Medium-chain triglyceride
NAFLD: Non-alcoholic fatty liver disease
25-OHD: 25-hydroxy vitamin D
OLGB: Omega-loop gastric bypass
RYGB: Roux-en-Y gastric bypass
SAT: Subcutaneous adipose tissue
UL: Tolerable upper intake level
VAT: Visceral adipose tissue
